### Intervention arms

#### Information to all study subjects

All participants will be advised about the importance of regular physical exercise and a balanced diet by a trained dietician before they receive the treatments. Importantly, they are instructed not to change their exercise or diet habits during the entire study period.

True acupuncture or sham acupuncture and metformin will be started 2 days after the baseline visit including OGTT and Ins. All subjects will be asked to use a barrier method for contraception. True and sham acupuncture treatment will be given three times per week. Each treatment session lasts for 30 min and can be separated by an interval of 1-3 days, with a maximum of 48 treatment sessions during 4 months. After the third treatment, all patients fill in the expectation and credibility questionnaire [31]. Metformin (0.5 g per pill) or placebo will be given, three times per day for 4 months.

### True acupuncture protocol

The rationale of acupuncture protocols is based on traditional Chinese and Western medical theories, and the study protocol follows the CONSORT [26] and Standards for Reporting Interventions in Clinical Trials of Acupuncture (STRICTA) [32] recommendations. We will use fixed acupuncture protocols. The acupuncture protocol of this randomized controlled trial (RCT) follows the protocol in the previous RCT in women with PCOS including *Acupuncture to Treat Insulin Resistance in Women With and Without Polycystic Ovary Syndrome* (ClinicalTrials.gov NCT01457209) [33], *Acupuncture and Clomiphene Citrate on Live Birth in Anovulatory Women With Polycystic Ovary Syndrome* (ClinicalTrials.govNCT01573858) [34], and a prospective pilot study of *the Effect of Acupuncture on Insulin Sensitivity Polycystic Ovary Syndrome* (ClinicalTrials.gov NCT02026323) [25].

Disposable, single-use, sterilized needles made of stainless steel, 0.25 × 30 mm and 0.30 × 40/50 mm (Huanqiu, Suzhou Huanqiu Acupuncture Medical Instrument Co., Ltd. 215002 Suzhou, China), will be inserted to a depth of 15–35 mm in segmental acupuncture points located in abdominal and leg muscles with innervations corresponding to the ovaries. Two sets of acupuncture points will be alternated every second treatment (Table 1 [25]). The first set consists of the conception vessel (CV) 3, CV 12, and stomach (ST) 29 bilaterally and in the muscles above the knee, ST34, and ST 33 bilaterally and below the knee, spleen (SP) 6, and ST 36. Needles will also be placed in extra-segmental acupuncture points that do not innervate the ovaries large intestine (LI) 4 bilaterally. In total, 14 needles will be placed, and all will be stimulated manually by rotating the needle to evoke needle sensation (de *qi*) once when inserted. The following points will be connected to an electrical stimulator (Export Abteilung, Schwa-Medico GmbH, [name]): CV 3 to CV 12, ST 29 bilateral, and ST 34 to ST 33 bilateral. Stimulations are given as low-frequency electric acupuncture (EA) of 2Hz, 0.3 ms pulse length, with an intensity adjusted to produce local muscle contractions without pain or discomfort. Needles not connected to the electrical stimulator will be manually stimulated to evoke needle sensation every 10 min, in total four times. The second set consists of 14 needles placed in segmental abdominal points and stimulated electrically: ST 27 bilaterally, CV 6 connected to CV 10; leg points: SP10 connected to a non-acupuncture point located 6 cun proximal to the patella as the medial border (electrical stimulation); SP 6 and liver (LR) 3 bilaterally (manual stimulation). Extra-segmental points are pericardium (PC) 6 bilaterally (manual stimulation).

**Table 1 Tab1:** Acupuncture protocol [25]

Point	Stimulation	location	Muscle	Innervation
Set 1				
Zhongji (CV3)	EA	4 cun caudal to the umbilicus	Fibrous tissue, linea alba	L1
Zhongwan (CV12)	EA	On the midline, 4 cun superior to the umbilicus	Fibrous tissue, linea alba	Th7-8
Guilai (bilateral) (ST29)	EA	1 cun cranial to the pubic bone and 2 cun lateral of the midline	M. rectus abdominis	Th6-12
Liangqiu (bilateral) (ST34)	EA	2 cun above the superior lateral border of the patella on the line connecting the anterior superior iliac spine found with the knee flexed	M. quadriceps femoris	Femoral nerve
Yinshi (bilateral) (ST33)	EA	3 cun above the superior lateral border of the patella on the line connecting the anterior superior iliac spine found with the knee flexed	M. quadriceps femoris	Femoral nerve
Sanyinjiao (bilateral) (SP6)	De *Qi* four times	3 cun proximal to the medial malleolus	Mm. flexor digitorum longus, tibialis posterior	L4–5, S1–2
Zusanli (bilateral) (ST36)	De *Qi* four times	On the anterior lateral side of the leg, 3 cun below Dubi (ST35), one finger width (middle finger) from the anterior crest of the tibia	Musculi tibialis anterior	L4–5, S1
Hegu (bilateral) (LI4)	De *Qi* four times	On the highest point at m. interosseus dorsalis	Mm. interosseus dorsalis I, lumbricalis II, adductor pollicis	C8, Th1
Set 2				
Daju (bilateral) (ST27)	EA	3 cun cranial to the pubic bone and 2 cun lateral to the midline	M. rectus abdominis	Th6–12
* Qi*hai (CV6)	EA	1.5 cun caudal to the umbilicus	Fibrous tissue, linea alba	Th11
Xiawan (CV10)	EA	2 cun cranial to the umbilicus	Fibrous tissue, linea alba	Th8
Extra-meridian point (bilateral)	EA	6 cun above the patella in line with SP10	M. quadriceps femoris	L2–L4
Xuehai (bilateral) (SP10)	EA	With the knee flexed, on the medial side of the thigh 2 cun above the superior medial corner of the patella on the prominence of the medial head of the quadriceps muscle of the thigh	M. quadriceps femoris	L2–L4
Sanyinjiao (bilateral) (SP6)	De *Qi* four times	3 cun proximal to the medial malleolus	Mm. flexor digitorum longus, tibialis posterior	L4–5, S1–2
Taichong (bilateral) (LR3)	De *Qi* four times	Between metatarsal I & II, just distal to the caput	M. interosseus dorsalis I	S2–3
Neiguan (bilateral) (PC6)	De *Qi* four times	2 cun proximal to the processus styloideus radii, between the tendons of the palmaris longus and the flexor carpi radialis	M. flexor digitorum superficialis	C8, Th1

The two sets will be alternated for every other treatment

*C* cervical vertebra, *CV* conception vessel, *EA* electroacupuncture, *L* lumbar vertebra, *LI* large intestine, *LR* liver, *M.* musculi, *Mm.* musculus, *PC* pericardium, *S* sacral vertebra, *SP* spleen, *ST* stomach, *Th* thoracic vertebra

#### Needle insertion technique

Needle insertion should be gentle. The skin is tightened by pressing around the area of needle insertion, and the needle is then gently inserted.

#### Needles and stimulation

Needle size: 0.25 × 30 mm or 0.30 × 40 or 0.30 × 50 mm. Select needle length with respect to the patients’ BMI: 0.25 × 30-mm needles in women with normal BMI, 0.30 × 40-mm needles in overweight women, and 0.30 × 50 or 75-mm needles in obese women. Depth of insertion may vary from patient to patient. Needles are placed with a depth deep enough to reach muscle/fibrous tissue. When a needle is inserted, the needle is stimulated gently until de *qi* (needle sensation reflecting activation of sensory afferents). As soon as de *qi* has been reached, the needle does not hurt or cause any pain and discomfort. Manual stimulation of needles that are not attached to an electrical stimulator is stimulated when inserted, after 10 min, 20 min, and immediately before they are removed after 30 min.

The electrodes are attached to an electric stimulation according to the protocol. The electric stimulator is turned on to program 10, and the intensity is gradually increased. The intensity will be as high as possible without causing pain or discomfort of subjects. The stimulation amplitude/intensity will be adjusted after 10 and 20 min at the same time as when manually stimulated needles are manipulated. After 30 min the stimulator is turned off, electrodes are disconnected, and needles are taken out.

### Sham acupuncture protocol

Disposable, single-use, sterilized needles made of stainless steel, 0.20 × 20 mm (Huanqiu, Suzhou Huanqiu Acupuncture Medical Instrument Co., Ltd. 215002 Suzhou, China) will be inserted superficially to a depth of <5 mm, one in each shoulder and one in each upper arm at non-acupuncture points (Table 2 [34]) with no stimulation. Placement of needles is unlikely to affect ovulation and IR in women with PCOS. Electrodes will be attached to the needles, and the stimulator will be turned on at an intensity of zero (no active current) to mimic EA in the acupuncture protocol. No manual stimulation of the needles will be performed. An intended adjustment of the intensity is made after 10 min, 20 min, and again after 30 min when the stimulator is turned off and the needles removed.

**Table 2 Tab2:** Sham acupuncture protocol [34]

Point	Stimulation	location	Skin innervation
No known point	Sham EA	On top of acromion	C3-4, n. supraclavicularis
No known point	Sham EA	On humerus, behind LI14	C5-6, n. cutaneous brachii lateralis

### True and sham acupuncture treatment

Time of the day and the name of the acupuncturist when the patient receives acupuncture will be recorded.The intensity of stimulation (mA) is noted. It may vary between different electrodes. Note the range, e.g., 1.2 – 3.0 mA.Note any other events that may affect the treatment (positive or negative).Note concomitant medications.Collect menstrual logs at the end of every cycle.

### Metformin and placebo

Metformin (Bristol-Myers Squibb Co., Shanghai, China) and placebo tablets (Jaden Pharmaceutical Co., Ltd., Guangzhou, China) will be packed and tested by a commercial pharmacy supply company (Panlongyunhai Pharmaceutical Co., Kunming, Yunnan, China) specifically for this study. Metformin or placebo will be started 2 days after the baseline visit including OGTT and Ins. Subjects will take 0.5 g/time, three times per day for 4 months. If the patients have adverse effects such as nausea and dizziness, the dose will be reduced to 0.5 g/time, two times or one time per day according to the severity.

### Monitoring and examination during the treatment

All subjects will be instructed not to change their physical exercise habits or diet during the entire study. They are asked to use barrier contraception, not hormonal contraception. Physical examination will be performed monthly. Every menstruation should be recorded, including the date, volume, and duration of menstruation during the entire study and follow-up. The conditions of physical exercise and diet will be recorded for every cycle.

### Study-specific visits and procedures

Patients will attend five visits, including the screening visit, baseline measurements, treatment visit, after-treatment measurements, and follow-up measurements. Months indicate when each specific measurement takes place. Adverse events and concomitant medications will be recorded during every visit. The overview of study visits is shown in Table 3.

**Table 3 Tab3:** Overview of study visits

	Screening visit	Baseline visit	Month				Follow-up after 4 months of treatment	End of treatment visit 3 months after the last acupuncture treatment
			1st	2nd	3rd	4th		
OGTT and Ins		√					√	√
Body composition (weight, height, waist circumference, hip circumference, FG/acne)	√	√	√	√	√	√	√	√
Menstrual cycle diary	√	√	√	√	√	√	√	√
Fasting blood samples for FGLU, FINS, HbA1c, C-peptide, TSH, T3, free T4	√							
Fasting blood samples for FSH, LH, SHBG, T, E2, PRL		√					√	√
Fasting blood samples for ApoA1,ApoB, TC, TG, HDL-C, LDL-C, BRT, renal and liver profile		√					√	√
Transvaginal or transrectal ultrasound	√						√	√
Questionnaires		√					√	√

*Apoa1* apolipoprotein A1, *ApoB* apolipoprotein B, *BRT* blood routine test, *E2* estradiol, *FG* Ferriman-Gallwey score, ﻿*FGLU* f﻿asting blood glucose*, FINS* Fasting insulin, *FSH* follicle-stimulating hormone, *HbA1c* glycosylated hemoglobin, *HDL-C* high density lipoprotein, *LDL-C* low density lipoprotein, *LH* luteinizing hormone, *PRL* prolactin, *SHBG* sex hormone-binding globulin, *T* total testosterone, *TC* total cholesterol, *TG* triglyceride, *TSH* thyroid stimulating hormone, *T3* triiodothyronine, *T4 *thyroxine, *OGTT* oral glucose tolerance test, *Ins* insulin-releasing test

### Screening visit

Women are screened in the morning after an overnight 12-h fast. Detailed information about the study design is given.

#### Obtain signed informed consent

##### Complete physical examination

Complete physical examinations will be performed including height, weight, hip, and waist measurements. Height and weight will be recorded to the nearest 0.1 cun and 0.1 kg, respectively. Waist and hip circumference will be recorded to the nearest 1 cun. Hirsute assessment by FG, acne standard acne lesion counts, and pelvic examination will be conducted.

#### Perform transvaginal or transrectal ultrasound of ovaries

Ovaries, including the ovarian size in three dimensions, the size of the largest ovarian follicle/cyst and size of every follicle with a mean diameter greater than 10 mm, and total antral follicle count (small follicles with mean diameter <10 mm) of each ovary will be obtained through transvaginal or transrectal ultrasound.

#### Check urine pregnancy test

##### Fasting blood samples to exclude other endocrine disorders

Fasting (at least 4 h) blood samples are taken to exclude any endocrine disorders:

Fasting glucose, fasting insulin, HbA1C (>7%), C-peptide, TSH (<0.2 mIU/ml or >5.5 mIU/ml), T3 (<1.4 nmol/l or >2.2 nmol/l), and free T4 (<10 pmol/l or >23 pmol/l).

#### Progestin withdrawal

Provide progestin prescription to induce withdrawal bleeding, with instructions to begin medication once eligibility has been determined.

### Baseline visit

After the screening visit, if a woman fulfills inclusion criteria and has signed the informed consent form, she will be assigned to the baseline visit. The baseline visit takes place day 2–5 of a spontaneous period or after a withdrawal bleeding after an overnight fast.

#### Laboratory Examination

Blood will be collected. Part of it will be stored, and the remainder is used for determination of DNA and sphingolipid levels.
*Circulating sex steroids:* Fasting serum levels of follicle-stimulating hormone (FSH), luteinizing hormone (LH), estradiol (E2), prolactin (PRL) and T, and sex hormone binding globulin (SHBG).
*Lipid profile:* Triglycerides (TG), total cholesterol (TC), high-density lipoprotein (HDL-C), low-density lipoprotein (LDL-C), apolipoprotein A1 (ApoA1), apolipoprotein B (ApoB), blood routine test﻿(BRT), and renal and liver profiles.
*Glucose homeostasis and insulin sensitivity:* The OGTT and Ins with 75 g glucose. Blood samples will be obtained to measure plasma glucose, serum insulin, and C-peptide at 0, 60, and 120 min during the OGTT and Ins.

#### Complete questionnaires

Quality of life will be assessed by the short form 36 (SF-36) [35], the Chinese Quality of Life (ChiQOL) [36], sleeping questionnaires [37], international physical activity questionnaire (IPAQ) [38], questionnaire of eating and weight patterns (QEWP) [39], and the Polycystic Ovary Syndrome Questionnaire (PCOS-QOL) [40]. We will also assess symptoms of anxiety and depression by the Zung SAS and Zung SDS questionnaires and complete the quantization table of traditional Chinese medicine (TCM) syndromes about PCOS.

#### Assess TCM syndromes of patients

Syndrome differentiation (Bian Zheng) in TCM is the comprehensive analysis of clinical information gained by the four main diagnostic TCM procedures: observation, listening, questioning, and pulse analysis, and it is used to guide the choice of treatment by acupuncture and/or TCM herbal formulae [41]. In PCOS, patients are empirically differentiated into four categories: (1) phlegm-dampness syndrome, (2) blood stasis syndrome, (3) phlegm, and (4) blood stasis.

### Visit after 4 months of acupuncture treatment

During the end of treatment visit, all baseline measures will be repeated as listed below:Physical examination will be performed, including vital signs, height, weight, and hip and waist measurements as well as repeating hirsute and acne assessments after the end of treatment or pregnancy.The serum levels of sex hormone steroids and the metabolic profile will be repeated.The transvaginal or transrectal ultrasound will be repeated for antral follicle counts.OGTT and Ins will be repeated.Blood will be collected for storage and for determination of DNA and sphingolipid levels.QOL, sleeping, IPAQ, anxiety/depression questionnaires, QEWP, and the quantization table of TCM will be repeated.Menstrual logs will be collected.Adverse events and concomitant medications will be recorded.The questionnaires about acupuncture treatment will be answered.

### End of treatment visit

The end of treatment visit will be done 3 months after the last acupuncture treatment (see points 1-8 under Visit after 4 months of acupuncture treatment). All the subjects will be followed up by visiting the acupuncturists monthly for 3 months. The conditions of physical exercise and diet will be record every month.

### Safety analysis

Adverse events will be categorized and the percentage of patients experiencing adverse events and serious adverse events during the treatment period and follow-up period will be documented and reported to the Data and Safety Monitoring Board (DSMB). These will be reviewed on a quarterly basis by the DSMB, and serious adverse events will be immediately reviewed.

### Outcome measures

#### Primary outcome

Change in HOMA-IR.

#### Secondary outcomes

Improvement rate of HOMA-IR.HOMA-β: Islet β-cell function will be evaluated by the formula (20 × fasting insulin (mU/ml) / (fasting plasma glucose (mmol/l) − 3.5)) [42] and by the C-peptide index (CPI) Fasting C-peptide (nmol/l)/f-glucose (mmol/l) × 100 [43].The insulin response to glucose will be assessed by calculating the area under the curve during the OGTT and Ins performance for glucose (AUCglu) and insulin (AUCins) using the trapezoidal rule [44].Frequency of menstrual cycles and ovulation.Body composition: weight, BMI, waist-to-hip circumference, and FG and acne lesion counts.Metabolic profile: glucose and insulin concentrations, C-peptide, HbA1c, TC, TG, HDL-C and LDL-C, and ApoA1 and ApoB.Hormonal profile: FSH, LH, T, and SHBG.Questionnaires: SF-36, ChiQOL, sleeping questionnaires, IPAQ,QEWP, PCOS-QOL, Zung SAS, Zung SDS questionnaires, and the quantization table of TCM syndromes about PCOS will be used to assess the quality of life and sleep and the emotional state and to measure the moderate physical activity.Side effect profile.Expectation and credibility of treatment.

### Data management and quality control of data

Both the Case Record Form (CRF) and web-based electronic database will be used to manage individual participant data. Quality control of the data will be handled at two different levels: the investigators will be required to ensure the accuracy of the data as the first level of control when they input the records in CRF. The second level will include data monitoring and validation that will be carried out by an independent group. A web-based electronic database, ResMan (www.medresman.org), is used as a double input database. Finally, the individual participant data except the private information will be allowed to be share with the public within 6 months after the trial completion.

### Sample size calculations

In our pilot study [25] evaluating the effect of acupuncture on insulin sensitivity in PCOS women with IR, HOMA-IR reduced significantly after 3 months of acupuncture treatment when an interim analysis was performed and changed from (4.3 ± 2.5) vs. (3.7 ± 2.1). HOMA-IR ≥2.14 was considered to be abnormal. We anticipate that the HOMA-IR after 4 months of true acupuncture treatment will decrease 25%, and sham acupuncture will be decreased 5% as it is well known that sham is not an inert procedure. Therefore, the difference is 20%, with two-sided α assigned to be 5% and β 20% at the upper limit, respectively, at which the power is 80% and the rate of attrition estimated to be 20%. Thus, the sample size has been inflated from 95 to 114 per group, totaling 342 cases for the three arms. The sample size was calculated using the software statistics toolkit supported by the Department of Obstetrics and Gynecology of the Chinese University of Hong Kong (http://www.obg.cuhk.edu.hk/ResearchSupport/StatTools/index.php).

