### Objectives

The primary objective of this randomized controlled trial is to evaluate the hypothesis that true acupuncture + metformin placebo (group 1) improves insulin sensitivity, as measured by changes in the homeostasis model assessment of insulin resistance (HOMA-IR), more effectively than sham acupuncture + metformin (group 2) and sham acupuncture + metformin placebo (group 3) in women with PCOS and IR. Secondary objectives include changes in HOMA-β (islet β-cell function), C-peptide index, the insulin response to glucose calculated from the oral glucose tolerance test (OGTT) and insulin releasing test (Ins), frequency of the regular menstrual cycle and ovulation, circulating sex steroids, lipid profile, health-related quality of life and symptoms of anxiety and depression, side effects, and credibility.

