### Statistical analysis strategy

The Kolmogorov-Smirnov test will be used to test the normal distribution of continuous variables. Continuous variables will be presented by mean ± standard deviation if they are normally distributed or by median with interquartile range if they are not normally distributed. Both per protocol (PP) analysis and intention-to-treat analysis (ITT) will be used to determine the robustness of the evidence. Analysis of variance (ANOVA) with Bonferroni corrections will be used for comparing the differences between groups of continuous data in accordance with a normal distribution or Kruskal-Wallis test for non-normal distribution data when appropriate; χ^2^ tests will be used for comparison of dichotomous data. For the primary outcome, analysis of covariance (ANCOVA) (accompanying LSMEAN and 95% CI) will be used. ANOVA will be used to calculate the changes from baseline to after treatment and follow-up, respectively, and it will also be used to compare the differences between treatment arms with respect to the primary outcome, HOMA-IR. Effect of continuous data will be reported by both *P*-value and mean difference with 95% confidence interval and categorical data by *P*-value and relative risk (RR) and risk difference (RD) with 95% confidence interval; the number needed to treat (NNT) will be calculated if there is statistical significance between groups. All statistical analyses of the data will be performed by using SPSS software version 21.0 (SPSS Inc., Chicago, IL, USA).

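### The 80% power covers only true versus sham acupuncture; the primary hypothesis also requires superiority over metformin, for which no effect or power is given

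*Protocol article*

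**What the plan says.** **Hypothesis.** The Objectives section states that true acupuncture plus metformin placebo (group 1) is to improve HOMA-IR "more effectively than sham acupuncture + metformin (group 2) and sham acupuncture + metformin placebo (group 3) in women with PCOS and IR". The end of the Background puts it the same way, as superiority to metformin and to sham.

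**Sizing.** The section on sample size calculations gives one pair of responses: "We anticipate that the HOMA-IR after 4 months of true acupuncture treatment will decrease 25" per cent, against 5% for sham. It concludes "Therefore, the difference is 20" per cent, and then sizes the trial "with two-sided α assigned to be 5% and β 20% at the upper limit, respectively, at which the power is 80" per cent. The result is 95 per group, raised to 114 for attrition, 342 in all. No response is given for the metformin arm and no difference to detect against it. The only variability shown is the pilot's, where HOMA-IR "changed from (4.3 ± 2.5) vs. (3.7 ± 2.1").

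**Analysis.** The statistical analysis strategy says "Analysis of variance (ANOVA) with Bonferroni corrections will be used for comparing the differences between groups of continuous data". It then names ANCOVA for the primary outcome with no correction attached, and later says that ANOVA will also compare the arms on HOMA-IR. The number of contrasts to be corrected for is not given.

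**The concern.** A power statement should refer to the hypothesis that the trial sets out to test. Here the hypothesis has two parts and the calculation covers one. A reader who sees 80% power and 342 patients in three arms will take it that the comparison with metformin is powered too. The Discussion encourages this by saying that the larger sample, controlled by both sham and an insulin-sensitizing drug, lowers the risk of a type II error.

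The Background describes metformin as an agent already used against insulin resistance in PCOS. Treating it as equal to sham is therefore an assumption that the protocol would have to state. If metformin has an effect of its own, the difference left for acupuncture to show is smaller than 20 points and the power against metformin falls quickly.

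The type I error rule is also unsettled. The sizing uses an undivided 5%, while the analysis section has a Bonferroni rule that may or may not reach the primary outcome.

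**Working it through.** **Inputs.** From the sample size section: true acupuncture 25% fall, sham 5% fall, baseline mean 4.3, pilot SDs 2.5 (before) and 2.1 (after), two-sided 5%, power 80%. The section does not say which SD was used. From the section on randomization: allocation 1:1:1.

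**1. The plan's own figure.** Difference = 0.20 × 4.3 = 0.86. With SD 2.1,

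n = 2 × SD² × (z₀.₉₇₅ + z₀.₈₀)² / difference² = 2 × 4.41 × (1.960 + 0.842)² / 0.7396 ≈ 94.

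The t-test version gives 94.6, rounded up to 95, which matches. SD 2.5 would need 134, so 2.1 is inferred to be the value used. At 95 per group the standard error of a difference is 2.1 × √(2/95) = 0.305, and the t-test power is 80.2%.

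**2. Difference detectable against metformin.** All arms are of equal size, so with 95 per group and 80% power it is also about 0.86 units, or 20 percentage points. With a 25% fall on true acupuncture, that is met only if metformin lowers HOMA-IR by no more than 25 − 20 = 5%, the sham figure.

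**3. Power for the stated hypothesis, no correction.** The difference against metformin is (25% − m) × 4.3, where m is the metformin fall. The two test statistics share the true-acupuncture arm, so they have correlation 0.5. Joint power was found by simulation with t-tests, 95 per group, SD 2.1. The values of m are assumptions.

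| m (assumed) | Difference vs metformin | Power vs metformin alone | Power to win both |
|---|---|---|---|
| 5% (same as sham) | 0.86 | 80% | 69% |
| 10% | 0.645 | 56% | 50% |
| 15% | 0.43 | 29% | 27% |
| 20% | 0.215 | 11% | 10% |

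A normal approximation gives 70%, 51%, 28% and 10% for the last column.

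**4. If Bonferroni is applied to the primary contrasts.** Power for true versus sham at 95 per group, without baseline adjustment:

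- two contrasts (0.025 each): 71%; 115 per group would be needed for 80%;
- three contrasts (0.0167 each): 66%; 127 per group would be needed.

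**5. Possible gain from ANCOVA.** Adjustment for baseline multiplies the SD by √(1 − r²). With r = 0.5, an assumption, the SD becomes 2.1 × √0.75 = 1.82. True-versus-sham power is then 90% at 5%, 84% at 0.025 and 80% at 0.0167. Joint power at 5% (normal approximation) becomes about 84% if metformin equals sham, and 65%, 36% and 12% for metformin falls of 10%, 15% and 20%.

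**The case against.** Several objections have weight.

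- **The 80% is not a wrong number.** The section ties it to the true-versus-sham difference, and for that contrast it reproduces. This stands. The fault is that the contrast is narrower than the hypothesis.
- **Bonferroni on the primary outcome is implied, not stated.** A reader might infer that the primary analysis is Bonferroni-corrected and so has only 71% or 66% power. The text does not support this as a fact: the correction is attached to ANOVA, ANCOVA is named for the primary outcome without one, and the number of contrasts is missing. If success requires both contrasts, each may be tested at 5% and no split is needed. The 71% and 66% are conditional.
- **ANCOVA may restore the loss.** At SD 2.1 a baseline correlation of about 0.5 offsets the Bonferroni loss on the sham contrast. It would also lift joint power above 80% if metformin equals sham. The protocol states no correlation and claims no such gain. Even with it, joint power is about 65% or less once metformin lowers HOMA-IR by 10% or more.
- **The metformin contrast need not be uninformative.** The plan reports mean differences with 95% intervals. At 95 per group and SD 2.1 the half-width is about 1.96 × 0.305 = 0.60 units, which says something about metformin whatever the P-value. Nor does the protocol propose to read a null result as equivalence.
- **The pilot does not refute the effect size.** A reader might set the pilot's fall of (4.3 − 3.7)/4.3 = 14% against the 20-point difference. That fall was uncontrolled and at 3 months; its counterpart is the 25% assumed at 4 months. It is a separate caution about optimism.

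**Conclusion.** The concern holds in this form: the stated 80% power applies to true versus sham acupuncture at an unadjusted two-sided 5%, and not to the primary hypothesis of superiority over both comparators. With the plan's own inputs, no correction and no ANCOVA gain, power for that hypothesis is at most about 69% if metformin does at least as well as sham. It is about 50%, 27% or 10% for assumed metformin falls of 10%, 15% or 20%.

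The figures rest on SD 2.1, inferred because it reproduces 95, and on a metformin range that is not in the document. The further loss from Bonferroni is conditional on a rule that the analysis section leaves unclear. The missing metformin assumption depends on neither the Bonferroni nor the ANCOVA question, and it is the part that has to be corrected.

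**What to change.** **Sample size calculations.** State that the 80% power applies to true versus sham only. State that the difference detectable against metformin with 80% power at 95 per group is about 0.86 HOMA-IR units (20 percentage points). Name the SD used. Give the joint power over a stated range of metformin responses, as in the table above.

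**Statistical analysis strategy.** For the primary outcome, replace the unclear Bonferroni rule by a fixed sequence on the ANCOVA contrasts: true versus sham at two-sided 5%, then true versus metformin at two-sided 5% only if the first is significant. This controls the type I error across the two claims and matches the undivided 5% used for sizing. Add that a non-significant contrast with metformin will not be read as equivalence.

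**Cost.** Wording in two sections, no extra patients. The Trial status section reports recruitment as ongoing, so the change belongs before unblinding. The downsides are that the stated power looks less favourable and that the metformin claim depends on first winning against sham. The change does not raise the power against metformin; it states it.

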**Methods:**

This study is a multi-center, controlled, double-blind, and randomized clinical trial aiming to evaluate the effect of acupuncture on the insulin sensitivity in PCOS combined with IR. In total 342 patients diagnosed with PCOS and IR will be enrolled. Participants will be randomized to one of the three groups: (1) true acupuncture + metformin placebo; (2) sham acupuncture + metformin, and (3) sham acupuncture + metformin placebo. Participants and assessors will be blinded. The acupuncture intervention will be given 3 days per week for a total of 48 treatment sessions during 4 months. Metformin (0.5 g per pill) or placebo will be given, three times per day, and for 4 months.

Primary outcome measures are changes in homeostasis model assessment of insulin resistance (HOMA-IR) and improvement rate of HOMA-IR by oral glucose tolerance test (OGTT) and insulin releasing test (Ins). Secondary outcome measures are homeostasis model assessment-β (HOMA-β), area under the curve for glucose and insulin, frequency of regular menstrual cycles and ovulation, body composition, metabolic profile, hormonal profile, questionnaires, side effect profile, and expectation and credibility of treatment.

Outcome measures are collected at baseline, at the end of treatments, and 3 months after the last acupuncture treatment. On completion of the screening visit, randomization will be conducted using a central randomization system.

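### The allowance for 20% attrition multiplies 95 by 1.20 instead of dividing by 0.80, so 114 per arm leaves about 91 evaluable rather than 95: a minor arithmetic error

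*Protocol article*

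**What the plan says.** The Sample size calculations section of the protocol article fixes the error rates "with two-sided α assigned to be 5% and β 20% at the upper limit", and gives "the rate of attrition estimated to be 20" per cent. The effect is set by anticipating that "HOMA-IR after 4 months of true acupuncture treatment will decrease 25%, and sham acupuncture will be decreased 5" per cent, a difference of 20 percentage points. The pilot figures quoted beside it are that HOMA-IR "changed from (4.3 ± 2.5) vs. (3.7 ± 2.1"); the text does not say which of the two SDs was used.

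The conclusion reads: "Thus, the sample size has been inflated from 95 to 114 per group, totaling 342 cases for the three arms". Attrition is the only reason offered for the step from 95 to 114. The total is repeated in the Methods part of the Abstract: "In total 342 patients diagnosed with PCOS and IR will be enrolled". Nothing elsewhere in the article revises either number.

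**The concern.** An attrition rate is a proportion of the women randomised. To be left with n evaluable after losing a proportion d, one must randomise n / (1 − d). Multiplying by (1 + d) always gives too few, because the loss then applies to the enlarged group.

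The figure 114 looks like the second calculation. If so, three numbers in the same paragraph conflict: 95 needed per arm, 20% lost, 114 randomised. At the plan's own attrition rate every arm would end below the number on which the power statement rests. The paragraph also treats β of 20% as an upper limit, so a shortfall goes in the unwelcome direction.

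**Working it through.** **Inputs from Sample size calculations.** Two-sided α 5%; power 80%; attrition 20%; decreases of 25% (true) and 5% (sham); pilot HOMA-IR 4.3 (SD 2.5) before and 3.7 (SD 2.1) after treatment; 95 per group before inflation, 114 after, 342 in total.

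**Inputs that I assume.** An absolute difference of 0.20 × 4.3 = 0.86, and an SD of 2.1 or 2.5. The article states neither choice.

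**1. Reproduce the base of 95.** For an unadjusted two-sample t-test with difference 0.86, SD 2.1, two-sided α 0.05 and power 0.80, the required size is 94.57 per arm, rounded up to 95. With SD 2.5 the same calculation gives 133.6, which does not match. The SD of 2.1 is therefore the likely input, but this is an inference.

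**2. Reproduce 114.**
- n × (1 + d) = 95 × 1.20 = 114.0, and 3 × 114 = 342. This matches exactly.
- n / (1 − d) = 95 / 0.80 = 118.75, so 119 per arm, and 3 × 119 = 357. This does not match.

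**3. What 114 delivers.**
- At 20% attrition: 114 × 0.80 = 91.2, about 91 evaluable per arm, about 4 fewer than 95.
- Largest attrition that still leaves 95: 1 − 95/114 = 16.7%.
- Check on 119: 119 × 0.80 = 95.2, which meets the requirement.
- Difference in numbers randomised: 119 − 114 = 5 per arm, 357 − 342 = 15 in total.

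**4. Effect on power for true versus sham acupuncture** (unadjusted two-sample t-test, two-sided α 0.05, difference 0.86):

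| SD assumed | 95 per arm | 91 per arm | Loss |
|---|---|---|---|
| 2.1 | 80.2% | 78.5% | 1.7 points |
| 2.5 | 65.5% | 63.6% | 1.9 points |

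The loss is just under 2 points under either SD. The level depends heavily on the SD, but that is a question about the base of 95 and not about the inflation.

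**The case against.** **The loss is trivial beside the uncertainty in the inputs.** This stands as to size. Moving between the two pilot SDs shifts power at 95 per arm by 80.2 − 65.5 = 14.7 points; the inflation error shifts it by less than 2. The point is a correction to a sentence, not a threat to the design.

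**Power may not actually fall below 80%.** This stands in part. The Statistical analysis strategy section names ANCOVA for the primary outcome, whereas 95 reproduces as an unadjusted comparison. If adjustment for baseline reduces the variance by the factor 1 − r², then with SD 2.1 and 91 per arm a correlation r of 0.2 gives 80.1% and r of 0.5 gives 88.7%. The article gives no correlation, so these values are illustrative, and the same section also names ANOVA for comparing the arms on HOMA-IR. The section plans an intention-to-treat analysis as well, so the number analysed could exceed 91. A reader might infer from the shortfall that the stated size, attrition and power cannot all hold together. The documents do not support that for power; they support it only for the evaluable number: 95 cannot remain from 114 after a 20% loss.

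**The error is far more serious once Bonferroni is applied.** A reader might combine the shortfall with a correction over three contrasts (α 0.0167) and quote power of about 64%. With difference 0.86 and SD 2.1, power at that α is 65.8% with 95 per arm and 63.5% with 91, so the inflation accounts for only about 2 points and multiplicity for the rest. The divisor of three is also not in the article: Objectives names two comparisons, and Statistical analysis strategy mentions Bonferroni corrections without giving a number. That figure does not measure this error.

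**114 might come from a stricter α.** The normal-approximation formula with two-sided α 0.025, difference 0.86 and SD 2.1 also gives 114. The text, however, states α of 5% and describes the step as inflation after naming attrition. On the other reading there would be no attrition allowance at all.

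**Conclusion.** The point holds as a minor arithmetic error. An allowance for 20% attrition from a base of 95 is 119 per arm (357 in total), not 114 (342). The printed size leaves about 91 evaluable per arm at the stated attrition, about 4 short of 95, and covers attrition only up to 16.7%. These statements use only figures printed in the article.

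The cost in power, a little under 2 points, is conditional: it assumes an unadjusted t-test, a difference of 0.86 and an SD of 2.1 or 2.5, none of which the article states as its inputs. Whether power in the planned analysis falls below 80% cannot be settled from the document. Neither the choice of SD nor multiplicity forms part of this finding.

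**What to change.** Keep 342 and restate the last step of Sample size calculations along these lines: *114 per arm retains the required 95 with up to 16.7% attrition; at 20% attrition about 91 per arm are evaluable.* This wording needs no assumption beyond the printed numbers.

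Do not simply replace 80% by a figure of about 78%. Any restated power should appear only together with the SD, the difference and the α behind it. If the sample size is reopened for other reasons, compute the inflation as n / (1 − 0.20), which gives 119 per arm from a base of 95.

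The cost is one sentence and a slightly less favourable attrition statement. No further patients are needed and nothing in the conduct of the trial changes. Trial status reports 114 of the planned 342 randomised by the end of December 2016, with recruitment continuing, so the sentence could be corrected before the final report.
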